**Patient/User Group Involvement**

We do not believe this research would benefit from patient group involvement at this stage, but it is possible that future research may well benefit from such involvement.

**Limitations**

As mentioned above, it is likely that patients receiving surgery, pharmacological treatment or no intervention are likely to differ substantially. We will attempt to account for this by using propensity score matching, though we acknowledge that this may have an impact on power if few matches are available. Until the data are available we cannot predict the extent of this limitation.

Some patients may pay for their own surgical treatment abroad, which may not be instantly recorded by their GP, or in extreme cases may not be recorded at all. This could lead to a misclassification of exposure in the non-treatment group, though it is anticipated this will only affect a minority of this group.

Similarly orlistat is available over the counter and such use will not be well captured in primary care data. We will therefore conduct a sensitivity analysis of the effects of orlistat, censoring at the time the license first allowed over the counter sales (early 2009)

Data are likely to be missing for a small number of patients on some variables (e.g. smoking, alcohol consumption and BMI). For smoking and alcohol, missing values will be treated as a separate stratum during the construction of the propensity score. For BMI, we anticipate mostly complete recording as it is fundamental to the care of this patient group. However, in rare cases of missing post-index BMI measures, these patients will be excluded from the analysis for changes in BMI.

**Plans for disseminating and communicating study results**

We intend to publish our findings in a peer reviewed journal and also to present them at relevant scientific conferences**.**

**Amendment**

A number of amendments to this protocol are now sought:

1. Due to funding constraints, it will not be possible to access QRESEARCH data and the study will be restricted to CPRD data only. We do not anticipate major changes to the feasibility of the study, as the current number of patients in the CPRD with bariatric surgery is now >3,000.
2. Following initial data processing it became apparent that matches for bariatric surgery patients, drawn from the population of patients with a BMI >30 were very dissimilar from the surgery patients, mainly because the surgery group tended to have a much higher BMI. Since the guidelines for surgery include a requirement of BMI >=40 in most instances, we propose matches to be drawn from a pool of patients with any measure of BMI >=40 during their registration.
3. For the analysis of weight loss, we intend to measure the effects to a maximum of three years post-intervention, largely driven by the amount of follow up available for surgery patients
4. Following statistical advice from [name], it was decided that mixed effects linear regression should be used to assess changes in weight and BMI over time within each group. We anticipate a non-uniform rate of change over follow up and will model this using splines. The Akaike Information Criterion (AIC) will be used to determine optimal spline knot points. From the final model, weight/BMI and 95% confidence intervals for the study population will be estimated. The rate of change in weight or BMI and 95% confidence intervals will be calculated for each spline component.
5. For all other outcomes, orlistat patients will be censored at the end of follow up, analogous to an intention to treat type analysis, so the long term consequences of the decision to start a course of treatment with orlistat can be measured, regardless of subsequent treatment. As a sensitivity analysis, follow up will be censored at the estimated date treatment was stopped, based on prescribing records.
6. Subgroup analyses according to underlying diabetes and cardiovascular disease status will be carried out, in line with NICE recommendations for research on treatments for obesity. Additionally, where numbers permit, analyses of bariatric surgery patients will be stratified by surgery type.
7. As a clarification, patients who have bariatric surgery and later receive orlistat will be excluded from orlistat analyses only.
8. We intend to divide the study into two separate research papers; one addressing changes in weight and BMI, and the other addressing all other outcomes.
9. **ADDITIONAL AMENDMENT 22 MAY 2014:** We plan to compare the risk of cardiovascular events in patients prescribed sibutramine with those prescribed orlistat. Sibutramine marketing was suspended in 2010 due to an increased risk of adverse cardiovascular outcomes. A review by the European Medicines Agency, found an “increased risk of non­fatal myocardial infarction and stroke, which outweighed the possible benefits of the medication through weight­loss” (Williams, 2010)[2]. This risk was clarified by the Sibutramine Cardiovascular Outcomes Trial (SCOUT; James et al, 2010), which examined cardiovascular outcomes in those at increased risk of cardiovascular events (i.e. individuals with diabetes mellitus, pre­existing cardiovascular disease or both). SCOUT randomized over 10,000 patients to either sibutramine or placebo. The primary outcome was time from randomization to non­fatal myocardial infarction, non­fatal stroke, resuscitation after cardiac arrest, and cardiovascular death. The risk of a primary outcome event was increased by 16% in the sibutramine group compared with placebo (hazard ratio, 1.16; 95% confidence interval [CI], 1.03 to 1.31; P=0.02), with overall incidences of 11.4% and 10.0%, in the two groups, respectively. This increase in primary outcome events was made up of non­fatal cardiovascular events, rather than cardiovascular death (hazard ratio, 0.99; 95% CI, 0.82 to 1.19; P=0.90). Also the increased risk was only shown in the groups with pre­existing cardiovascular disease (who previously had been excluded in prescribing guidance).

Orlistat remains the only prescribed drug for weight loss in the EU, and to date, no direct comparison has been made between orlistat and sibutramine regarding the risk of vascular outcomes. We will directly compare the risk of myocardial infarction and all cause mortality in patients prescribed orlistat and sibutramine. These outcomes are already included in this study, but the direct comparison between orlistat and sibutramine was not previously specified. This work will be done as part of an Epidemiology MSc summer project, by [name]. Specifically we will:

- 1. determine the relative risk of myocardial infarction (both fatal and non­fatal) in patients prescribed sibutramine or orlistat
  2. determine the relative risk of myocardial infarction in high­risk patients (i.e with cardiovascular risk factors) prescribed sibutramine or orlistat
  3. determine time to all­cause mortality in patients prescribed sibutramine or orlistat

1. Analysis plan

Initially, basic descriptive analyses of event rates will be conducted in each treatment group. Cox proportional hazard models will be used to investigate univariable and multivariable hazard ratios for the outcomes. Adjustment will be made for potential confounders (covariates to be assessed will include age, sex, weight, BMI, smoking status, alcohol consumption and a range of co-morbidities such as coronary heart disease, hypertension and diabetes). Following traditional regression analysis, propensity scores will be calculated to further explore possible prescribing biases and confounding, based on patient status with respect to the covariates listed above, and their orlistat/sibutramine exposure status. Our primary intention is to match sibutramine and orlistat patients with similar propensity scores, excluding any patients with scores in non-overlapping regions of the score distribution. Cox proportional hazards models will then be used to calculate Hazard Ratios for each outcome. Sensitivity analyses will also be used to estimate how large an effect an unknown confounder would need to have to eliminate or bring about any observed effect. We will also determine whether any effect is modified by age, sex, and area level social deprivation.

The cohort of obese patients already extracted contains over 27,000 patients prescribed sibutramine and 90,000 patients prescribed orlistat. Assuming a baseline 7% annual event rate (a two sided type I error rate of 0.05, and power set at 90%) to detect a 10% difference in hazard ratio between orlistat and sibutramine would require a sample size of 19,000 patients prescribed sibutramine and 58,000 patients prescribed orlistat. Assuming orlistat is not associated with an increased risk of vascular events, we estimate we have adequate power to detect an increased risk of MI, similar to the increased risk of MI and stroke detected in the SCOUT trial.

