**Study Design and Study Population**

A combination of two UK databases offers an excellent opportunity to study the clinical effects of interventions for obesity; the UK General Practice Research Database (GPRD) and QRESEARCH. In combination the GPRD and QRESEARCH contain information from >1100 UK general practices, and have current and historical data for >20 million patients. Continuous patient records include details of all consultations, diagnoses, prescribed medicines and basic demographic data. Patients are representative of the England & Wales population in terms of age, sex and geographical distribution [refs]. Data quality is subject to rigorous checks and audits and >500 peer reviewed studies have been published using GPRD or QRESEARCH data including studies investigating unintended effects of medication (GPRD, 2010; QRESEARCH, 2010). GPRD and QRESEARCH draw information from mutually exclusive practices and are therefore fully complementary.

*3.1 Study Design - Patient population, exposures of interest, inclusion/exclusion criteria*

The cohorts will comprise obese patients registered in the GPRD and QRESEARCH:

- Eligible patients will be those aged 18+ years with at least 12 months research standard registration time in the GPRD or QRESEARCH AND with one of the following exposures recorded by the study start:
  - A record of bariatric surgery with at least 12 months prior registration to ensure incident status (specific type of bariatric surgery used will be determined using data recorded in patient records); OR
  - A first prescription for orlistat with at least 12 months prior registration to ensure incident usage; OR:
  - A record of BMI>30 with neither bariatric surgery nor a prescription for orlistat – these patients will act as the **comparison group**
- The date of surgery or first orlistat prescription will be termed the index date. Each patient with surgery or orlistat will be matched with up to 5 obese patients without a record of these treatments, on age (within 5 years), sex and practice with at least 12 months research standard registration prior to the relevant index date.
- Patients will be followed until the earliest of; an outcome of interest, death, transfer out of the practice or last data collection date.

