**Statistical Analysis and Covariates**

*Baseline Comparisons*

We will use baseline data to compare the background characteristics of patients receiving surgical and pharmacological interventions for obesity with those receiving no intervention. This will give a broad picture of how these interventions are being targeted in the UK as a whole. Odds ratios and 95% confidence intervals will allow us to determine statistically and clinically relevant differences, using patients with no intervention as the baseline group. As a subgroup analysis, differences in the targeting of specific forms of bariatric surgery will also be determined. **Covariates** to be assessed will include age, sex, weight, BMI, smoking status, alcohol consumption and a range of co-morbidities such as coronary heart disease, hypertension and diabetes.

*Cohort analysis*

We will compare outcomes between patients receiving surgical and pharmacological interventions for obesity with those receiving no intervention. It is anticipated that these three groups of patients will differ in fundamental ways related to health outcomes that could represent important bias and confounding in this study. For this reason we will calculate propensity scores for each patient, capturing their likelihood to receive either surgery or a prescribed anti-obesity therapy. Using the propensity scores we will ensure comparisons are only made between patients with similar background characteristics (Sturmer et al, 2010). Cox proportional hazard regression will be used to conduct time to event analyses for death, diabetes, cardiovascular disease, fractures and liver disease, adjusting for the propensity score. Patients with no intervention will form the baseline group.

In addition, anonymised, linked Hospital Episode Statistic (HES) data are available for patients in the GPRD and will allow us to look in detail at hospital records for patients who undergo bariatric surgery (e.g. type of surgery, any complication that arise).

Patients who receive orlistat and later have surgery will move from one exposure group to the other, according to current treatment. We anticipate that very few patients will receive orlistat following surgery and any patients who appear to do so will be excluded from the analysis.

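### The surgery comparator pool accepts a BMI of 40 or more recorded at any time in registration, so comparators can be selected on a reading taken after the matched index date

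*Protocol*

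**What the plan says.** The Study Design and Study Population section sets the time origin: "The date of surgery or first orlistat prescription will be termed the index date". It then describes the comparators: "Each patient with surgery or orlistat will be matched with up to 5 obese patients without a record of these treatments". Matching is "on age (within 5 years), sex and practice with at least 12 months research standard registration prior to the relevant index date". BMI is not a matching variable, and 12 months of prior registration is the only condition tied to the index date. The eligibility text in the same section asks for patients "with one of the following exposures recorded by the study start", but the protocol does not define that start.

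Item 2 of the Amendment section reports that the first matches, drawn from patients with BMI above 30, were poor, "mainly because the surgery group tended to have a much higher BMI". The remedy adopted is: "we propose matches to be drawn from a pool of patients with any measure of BMI >=40 during their registration". This is the current rule for surgery comparators. Registration covers time before and after the index date, and the rule does not say which part counts.

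The Statistical Analysis and Covariates section lists covariates "to be assessed will include age, sex, weight, BMI, smoking status, alcohol consumption and a range of co-morbidities" and gives the propensity score its purpose: "Using the propensity scores we will ensure comparisons are only made between patients with similar background characteristics". The Limitations section also speaks of propensity score matching. Neither section states the date of the BMI that enters the score.

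**The concern.** Follow-up of a comparator starts at the index date of the matched surgery patient. If the comparator enters the pool only because of a BMI recorded, say, two years after that date, death or transfer out during those two years would have kept the person out of the study. The time is counted as follow-up, yet no death could have been observed in it. The protocol plans no delayed entry that would remove it.

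The rule also weakens its own purpose. It was introduced to bring comparators closer to surgery patients in BMI, but it can admit people who were below 40 at index because they reached 40 later or had passed it years before.

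The pool serves every comparison of surgery with no treatment. For outcomes where surgery appears to have an effect, the amendment of 21 May 2015 applies the relative risks to the event rate in the non-surgery group and scales to 1.4 million people. An error in the comparator death rate would then enter both the relative risk and the rate it multiplies.

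**Working it through.** The protocol gives no figure for this selection effect, so there is none to reproduce. The reading of the text settles whether the gap exists. The arithmetic only shows how large its effect could be.

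**Reading.** Three places could close the gap.
- The matching rule ties registration to the index date, not the BMI reading.
- The phrase about the study start is undefined, is not the index date, and is not repeated in the amended rule.
- The propensity score concerns background characteristics, but the date of its BMI is not given.

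None of them requires the qualifying reading to come first.

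**Mortality: inputs.**
- Death rate λ = −ln(0.95)/4 = 0.01282 per year, from the 5% mortality over 4 years in Sample Size/Power Calculation.
- Exponential censoring with mean 4 years, rate μ = 0.25 (assumption).
- A share f of the candidate pool qualifies only after index, with the reading uniform over L = 3 years, and is kept only if still under follow-up at that time (assumption).
- Equal underlying risk in early and late qualifiers (assumption).

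**Mortality: formulas.** Let k = λ + μ = 0.2628.
- Probability that a late candidate is kept: p = (1 − e^(−kL))/(kL) = 0.692.
- Guaranteed event-free time per late candidate: m = [1 − (1 + kL)e^(−kL)]/(k²L) = 0.903 years.
- Time genuinely at risk per candidate: A = [(1 − f) + f·p]/k.
- Observed rate divided by true rate: A/(A + f·m).

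| f | A | A + f·m | Observed/true | Understated by | Rate ratio seen if truth is 1 | Rate ratio seen if truth is 0.78 |
|---|---|---|---|---|---|---|
| 10% | 3.688 | 3.778 | 0.976 | 2% | 1.02 | 0.80 |
| 20% | 3.570 | 3.751 | 0.952 | 5% | 1.05 | 0.82 |
| 30% | 3.453 | 3.724 | 0.927 | 7% | 1.08 | 0.84 |
| 50% | 3.218 | 3.670 | 0.877 | 12% | 1.14 | 0.89 |

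The 0.78 is the planned effect, 3.9%/5%. The last two columns divide 1 and 0.78 by the observed/true ratio. They are person-time rate ratios, used as a guide to the Cox result.

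With mean censoring of 2.4 years, the follow-up that the protocol gives for surgery patients, the same formulas give 0.971, 0.941, 0.910 and 0.845, an understatement of about 3%, 6%, 9% and 15%.

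**Weight and BMI: illustration, all inputs assumed.** BMI at index is normal with mean 36 and SD 5. Personal slopes have mean 0 and SD 0.8 per year, measurement SD is 1, and readings are yearly from 4 years before to 4 years after index (400,000 simulated people).
- Of those with any reading of 40 or more, 22% qualify only after index. Their mean 3-year BMI change is +3.18.
- The other 78% qualify at or before index. Their mean change is −0.87.
- Together: 0.22 × 3.18 − 0.78 × 0.87 ≈ +0.02.
- Half of the pool has an index reading below 40.

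The two distortions are each large and nearly cancel here. Other inputs would tip the balance either way.

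**The case against.** The best defence is that the protocol does not leave BMI at index to chance. BMI is a listed covariate, propensity scores are to confine comparisons to similar patients, and the Limitations section names propensity score matching. A comparator at BMI 38 would often fall outside the overlap with a surgery group of much higher BMI, so the share of late qualifiers analysed could be well below their share in the pool. It can also be said that the phrase about the study start was meant as each patient's own start of follow-up.

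Much of the first argument stands. A reader might infer that BMI at index is ignored altogether. That is true of pool entry and of the age, sex and practice matching, but not of the planned analysis. What the argument does not reach is the guaranteed survival: a score built on baseline values cannot undo selection on a later event. The second argument fails because the phrase is undefined and the amended rule refers to the whole of registration.

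Other stronger readings are also tempting and not supported.
- Selection need not use post-index readings. The rule permits them and does not require them.
- Non-fatal event rates are not shown to be understated. A myocardial infarction, fracture or diabetes diagnosis does not prevent a later BMI reading.
- It does not follow that surgery patients below 40 have no similar comparators. A pool defined by any reading can contain people below 40 at index.
- It is not established that the biases for death and weight run in opposite directions, since the weight bias has two opposing parts.
- A late first reading does not prove a low BMI at index. The patient may simply not have been measured earlier.

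**Conclusion.** The point holds as a defect in a stated rule. As written, item 2 allows surgery comparators to be selected on a measurement taken after follow-up has begun, and the planned propensity adjustment does not repair this.

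For mortality, guaranteed survival pushes the comparator rate down. The size is about 2% to 12% for late shares of 10% to 50% under the main assumptions. In this model that bias works against surgery and could hide part of the planned reduction. The late share is assumed throughout, and the calculation holds underlying risk equal. Patients who gain weight after index may be at higher risk, so the net direction for death is not certain either. For weight and BMI, neither size nor direction can be settled from the protocol.

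Confidence is high about the wording and its mechanism, and low about the size.

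**What to change.** Amend item 2 so that a comparator qualifies only if the most recent BMI on or before the matched index date, within a stated look-back, is 40 or more. State that the propensity score uses that same pre-index BMI. Keep the pool defined by any reading as a sensitivity analysis only, and report how many of its members qualify solely after index, which would replace the assumed shares above.

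Matching within a BMI caliper is a further design option and is not needed to close this gap. Selecting on a threshold will still leave some regression to the mean: in the illustration, those with an index reading of 40 or more change by −0.27 BMI units over 3 years. That residual does not depend on any future measurement.

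The cost is re-matching on data already extracted. Some surgery patients will have fewer than five comparators, which the matching rule already allows.

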**Exposures**

Exposures will be defined as follows:

- First record of bariatric surgery with at least 12 months prior UTS registration
- A first prescription for orlistat with at least 12 months prior registration to ensure incident usage
- A first prescription for sibutramine with at least 12 months prior registration to ensure incident usage

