For exposure to orlistat, follow up time will be censored 3 months after the date when prescribing information indicates treatment was stopped. This period allows for a degree of medication stockpiling and a treatment washout period. Similarly, follow up time for controls matched to orlistat recipients will be censored at the same date ensuring similar follow up in comparison groups.

Sensitivity analyses will stratify orlistat exposure on dose and duration using recorded prescribing information to estimate daily dose and duration of treatment.

Where possible, we will calculate number needed to treat (NNT) or number needed to harm (NNH) for clinical outcomes where a treatment effect is seen.

Linear regression will be used to compare changes in weight and BMI between surgical or pharmacological interventions and no intervention, adjusting for the propensity score. Changes will be calculated annually.

Similarly, a paired t-test will be used within each treatment group to determine changes in weight and BMI from baseline (pre-intervention). Changes will be calculated annually.

Absolute rates will also be determined for post-operative complications (post-operative haemorrhage, post-operative infection, ITU admission, re-admission to hospital and re-operation). Cox regression will be used to compare the hazard for each event between different types of bariatric surgery.

Initially the analysis will be done separately for QRESEARCH and GPRD data. It is anticipated the results will be very similar since the two datasets represent different samples of the same underlying population. Assuming the results are similar, data will be pooled, and a single analysis will be done, which will increase precision.

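### Sibutramine-orlistat comparison (Amendment, item 9): no end of exposure is set for sibutramine and no rule covers patients who take both drugs, so an on-drug MI harm would be pulled towards no difference, with no on-treatment check

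*Protocol*

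**What the plan says.** **General rule (Protocol, Study Design and Study Population).** "Patients will be followed until the earliest of; an outcome of interest, death, transfer out of the practice or last data collection date". Neither stopping nor switching treatment ends follow-up.

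**Exposure (Exposures).** Sibutramine exposure is "A first prescription for sibutramine with at least 12 months prior registration to ensure incident usage". A start is defined; an end is not.

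**Stop rule in the main text (Statistical Analysis and Covariates).** "For exposure to orlistat, follow up time will be censored 3 months after the date when prescribing information indicates treatment was stopped". Controls matched to orlistat users are censored on the same date. Sibutramine is not mentioned.

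**Change of group (same section).** "Patients who receive orlistat and later have surgery will move from one exposure group to the other, according to current treatment". Moves between sibutramine and orlistat are not covered.

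**Amendment, item 5.** For outcomes other than weight and BMI, "orlistat patients will be censored at the end of follow up, analogous to an intention to treat type analysis". The reason given is specific to orlistat: the long-term consequences of deciding to start it. The item continues: "As a sensitivity analysis, follow up will be censored at the estimated date treatment was stopped, based on prescribing records".

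**Amendment, item 9 (May 2014).** This adds a direct comparison of sibutramine with orlistat for MI and all-cause mortality, and notes that "Sibutramine marketing was suspended in 2010 due to an increased risk of adverse cardiovascular outcomes". Its own analysis plan covers Cox models, propensity-score matching and effect modification. Its sensitivity analysis concerns an unmeasured confounder: "Sensitivity analyses will also be used to estimate how large an effect an unknown confounder would need to have". It says nothing on end of exposure, stopping or switching.

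**The concern.** Item 5 suits the question it was written for, the consequences of starting orlistat. Item 9 asks whether one drug carries more MI risk than another, and was prompted by a safety suspension. Under the default rule, all time after a first sibutramine prescription counts as sibutramine time. Time after the 2010 suspension is very likely drug-free, or spent on orlistat, which item 9 describes as the only prescribed weight-loss drug left in the EU.

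If the harm acts mainly while the drug is taken, such time dilutes the contrast. A hazard ratio near 1 could then mean either no harm or a harm averaged over unexposed time. As written, item 9 contains no analysis that separates the two.

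**Working it through.** **1. The plan's own figure.** Item 9 gives 19,000 sibutramine and 58,000 orlistat patients for 90% power, two-sided 0.05, a 7% annual event rate and a 10% difference.
- A two-proportion calculation with one-year risks of 7.7% and 7% and allocation 58/19 gives 19,293 : 58,894.
- With hazard ratio (HR) 0.90, so a one-year risk of 1 − 0.93^0.9 = 6.32% against 7%, it gives 18,994 : 57,982.

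The stated figure is reproduced. It makes no allowance for sibutramine time off drug.

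**2. Inputs for the dilution check.**
- From item 9: a 7% annual rate; 27,000 sibutramine and 90,000 orlistat patients available; HR 1.16 from the cited randomised trial; and the assumption that orlistat does not raise vascular risk, so time off orlistat leaves that arm's hazard unchanged.
- Assumed: the share f of sibutramine person-time that is on drug (the documents give no treatment duration), a constant hazard, no effect after stopping, and no sibutramine use in the orlistat arm.

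HR 1.16 serves only as an illustrative size. In the source it is measured from randomisation, against placebo, for a composite cardiovascular outcome.

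**3. Averaged hazard ratio.** HR_avg = 1 + (HR − 1) × f
- f = 100%: 1.16
- f = 75%: 1 + 0.16 × 0.75 = 1.12
- f = 50%: 1 + 0.16 × 0.50 = 1.08
- f = 25%: 1 + 0.16 × 0.25 = 1.04
- f = 10%: 1 + 0.16 × 0.10 = 1.016

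**4. Power with one year of events.** Events D = 27,000 × 0.07 × HR_avg + 90,000 × 0.07. Sibutramine share p = 27/117, so p(1 − p) = 0.1775. Power = Φ(√(D × 0.1775) × ln HR_avg − 1.96).
- f = 100%: D = 8,492; power above 99%
- f = 75%: D = 8,417; power 99%
- f = 50%: D = 8,341; √(8,341 × 0.1775) × ln 1.08 = 2.96; power 84%
- f = 25%: D = 8,266; the same product with ln 1.04 is 1.50; power 32%
- f = 10%: D = 8,220; power 9%

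**5. Longer follow-up.** Off-drug years also bring events. At HR 1.04 over 4 years, D = 27,000 × (1 − e^(−0.07 × 4 × 1.04)) + 90,000 × (1 − e^(−0.07 × 4)) ≈ 28,800, and power is about 80%. So the loss of power can be largely recovered. The estimate itself stays at 1.04 rather than 1.16.

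**6. Both drugs.** If 5% of orlistat person-time were also on sibutramine (assumed), the f = 50% value becomes 1.08 / (1 + 0.16 × 0.05) = 1.071, and the f = 25% value 1.04 / 1.008 = 1.032. This is a small further move towards 1.

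**The case against.** **The initiator contrast is legitimate.** Item 9 asks about patients prescribed each drug, exposure is defined by first prescription, and comparing starters with an active comparator is a recognised design. On-treatment censoring has its own bias if patients stop because cardiovascular symptoms emerge. This stands. It is a reason to keep the initiator analysis and not to demote it.

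**Item 5 already has a stop-date analysis.** A reader might infer that the plan has only an intention-to-treat rule; the next sentence of item 5 shows otherwise. A reader might also infer that the plan stops the clock for orlistat but not for sibutramine. No passage states such an analysis for item 9. The documents support less: item 5 is worded for orlistat, item 9 does not take it up, and its reach is unclear. Extending it to sibutramine would still leave switching uncovered.

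**The size is assumed.** This stands. The documents give no treatment duration, switching rate or last data collection date, so a claim of about four drug-free years per patient is not supported. Nor is a claim that the comparison could hardly detect harm, given step 5 of the working.

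**A separate analysis plan may hold these rules.** That is possible. But the Protocol itself fixes the follow-up rules and gives item 9 an analysis plan, and those are what leave sibutramine on the default.

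**Conclusion.** The point holds in a limited form. In item 9, sibutramine has no drug-specific follow-up rule and falls to end-of-record follow-up by default. The stop-date sensitivity analysis of item 5 is not carried over, and patients who take both drugs are not addressed. If the harm wanes after stopping, the direction of the effect is towards a hazard ratio of 1. On the illustrative 1.16, that means about 1.08 with half of follow-up on drug and 1.04 with a quarter. The on-drug shares, the constant hazard and the absence of carry-over are assumptions; a lasting effect would mean less dilution.

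The main consequence lies in the estimate and its interpretation more than in power. The documents do not show that the initiator analysis is wrong, or that on-treatment follow-up must be primary. This is a worthwhile and inexpensive improvement to a secondary comparison.

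**What to change.** Keep the initiator (intention-to-treat type) analysis for MI and mortality. Add to item 9 a pre-specified on-treatment analysis of MI, applied identically to both drugs:
- Follow-up runs from first prescription to the estimated stop date plus the three-month window already in Statistical Analysis and Covariates.
- Censor earlier at a first prescription of the other drug or at bariatric surgery.
- State how patients who have already taken the other drug before entry are classified.

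Report both analyses side by side, with the share of person-time on drug in each arm. State in advance that a null initiator result alone will not be read as absence of on-drug harm. Also say explicitly whether the item 5 stop-date sensitivity analysis applies to sibutramine.

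**Cost:** protocol wording and one more run on prescribing records. The on-treatment analysis will have fewer events, and stopping may be informative; the retained initiator analysis is the counterweight to both.
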